#### 2.5.11. Criteria to Interrupt of Modify the Intervention

The intervention will be interrupted for the following situations: if a participant requests it due to discomfort, lack of time, or for any other reason; if serious adverse events directly related to the intervention compromise participant safety; if severe health issues arise that cannot be managed within the protocol, such as a serious illness, injury, or wound.

The research team will have the authority to suspend the intervention under these rules or for any other justified reason.

Modification of the intervention will be considered in the event of moderate adverse events that do not require the interruption of participation but justify a change, such as adjusting the psychoeducational content or reducing the emotional load.

Any modification will be preceded by a thorough evaluation to determine its feasibility and will be submitted to the relevant ethics and research committee before implementation, and informed consent will be obtained from the participants, clearly explaining the reasons and implications of the change. All modifications or interruptions of the protocol will be documented, specifying the reasons, the communication with the participants, and the nature of the corresponding action.

In the event that a participant experiences an adverse effect derived from the intervention, it will be documented in writing and reported to the research ethics committee; psychological attention or appropriate compensation will be offered to remedy any harm.

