Ill-Being (Burnout). The Athlete Burnout Questionnaire (ABQ) [25], validated for the Mexican context [26], will be used. It consists of 15 items on a Likert scale from 1 (*almost never*) to 5 (*almost always*), except for items 1 and 14, which are reverse-coded. It evaluates three burnout-related factors: reduced sense of accomplishment, physical and emotional exhaustion, and devaluation of sports practice. The scale has shown adequate reliability and validity [26]. Although this instrument was originally developed for athletic populations, its use in exercise and well-being promotion contexts is considered appropriate in the present study, given that, in addition to PsicoFIT, the program includes other components, such as football fitness, which involves sport-based physical activity, a framework in which burnout dimensions may be relevant for program participants, while acknowledging the limitations inherent in attributing potential changes exclusively to the psychoeducational intervention.

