#### 2.4.2. Football Fitness Training

The face-to-face modality includes, on a weekly basis, one hour of recreational training, two two-hour football-based exercise sessions, and 40 min of autonomous recreational physical activity.

The semi face-to-face modality also includes one hour of recreational training (face-to-face), two sessions averaging 24 min of high-intensity interval training (HIIT) through videos hosted through a digital platform, and 40 min of autonomous recreational physical activity per week.

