#### 2.6.4. Data Monitoring

The study will be overseen by the research team, which will verify protocol compliance, data confidentiality, and information safeguarding. Periodic internal meetings will be held to review progress, safety, and protocol adherence.

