The integration of this protocol within a broader program that includes three interventions and a coach training component implies that observed changes in the study variables may be influenced by the effects of other interventions. While efforts will be made to isolate the specific impact of the present intervention, the results may reflect interactions among different program components, although this problem can also be mitigated to some extent by including it within the same theoretical framework of self-determination, since theoretical coherence could ensure that the strategies, language, and techniques used, as well as the objectives, are consistent, facilitating implementation, acceptance by the participants, and maximizing the potential results [123]. Finally, it should be noted that the results are limited in their generalizability due to the nature of the participants: all of them are football fans, as well as the difference in the “dose” of the intervention between the modalities, which could influence comparative outcomes.

Based on everything discussed and the limitations expressed, it seems clear that the most relevant future development is the empirical application of the protocol in the most efficient way possible, as well as presenting the results obtained, to be replicated for verification and eventual validation as a useful psychoeducational intervention to meet the stated objectives.

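### Section 2.5.11 requires an adverse effect to be recorded only if it is judged to derive from an undefined intervention, and the two modalities differ widely in the chance to notice events

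*Protocol article*

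**What the plan says.** The last paragraph of Section 2.5.11 (protocol article) gives the recording rule: "In the event that a participant experiences an adverse effect derived from the intervention, it will be documented in writing". The same paragraph sends such an effect to the research ethics committee.

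One ground for interruption in that section also carries a causal condition: "if serious adverse events directly related to the intervention compromise participant safety". Others do not. A participant may ask to stop for any reason. Interruption also follows "if severe health issues arise that cannot be managed within the protocol, such as a serious illness, injury, or wound". And "The research team will have the authority to suspend the intervention under these rules or for any other justified reason". Modification may be considered for moderate adverse events, with no test of relatedness. Every interruption or modification is to be written up with its reasons.

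Section 2.5 opens by using the term intervention for the weekly PsicoFIT modules. Section 2.4 describes the rest of what participants receive under TIGREFIT: exercise, nutrition talks and trained coaches, delivered in parallel. In the semi face-to-face modality the exercise includes "two sessions averaging 24 min of high-intensity interval training (HIIT) through videos hosted through a digital platform". On oversight, Section 2.6.4 says "The study will be overseen by the research team", with periodic internal meetings that review safety among other things.

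**The concern.** A harm record is most useful when events are written down first and attributed later. Here the duty to record begins only after someone has decided that the event came from the intervention, and the article does not settle whether that means PsicoFIT or the whole programme. The examples of modification in Section 2.5.11 concern psychoeducational content and emotional load, which favours the narrow reading. Yet much of the physical risk for sedentary adults with a BMI of 28 to 34.9 plausibly lies in the exercise component.

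Two things are at stake. The periodic safety review and the modification rule can act only on events that are known. And if the recorded events are ever set side by side by modality, the counts would partly reflect how much time staff spent with each group.

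**Working it through.** The article states no adverse event rate, expected count or contact total, so there is no figure to reproduce. The check has three steps.

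**Step 1. Which events must be recorded under Section 2.5.11?**
- Judged to derive from the intervention: recorded and reported to the ethics committee.
- Judged not to derive from it, but leading to interruption or modification: that action is documented with its reasons, so the event enters the record by this route.
- Judged not to derive from it, and leading to neither: no duty to record is stated.

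Take a minor strain during a video exercise session after which the participant carries on. If the intervention means PsicoFIT, the strain falls in the third group. If it means TIGREFIT, it falls in the first. One event has two outcomes, depending on a definition that the article does not give.

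**Step 2. Opportunity to notice events.** Inputs per week, from Sections 2.4.2, 2.4.3 and 2.5:
- Face-to-face: 60 min recreational training, 2 × 120 min football-based sessions, a 30 min nutrition talk, a 30 min PsicoFIT session, and 40 min autonomous activity. Nutritional counselling has no stated length and is left out.
- Semi face-to-face: 60 min recreational training in person, 2 × 24 min video exercise, and 40 min autonomous activity. Nutrition and PsicoFIT come as videos.

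Scheduled in-person contact:
- Face-to-face: 60 + 240 + 30 + 30 = 360 min a week, or 6 h × 12 = 72 h over 12 weeks.
- Semi face-to-face: 60 min a week, or 1 h × 12 = 12 h.
- Ratio: 360 / 60 = 6.

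Share of prescribed exercise time spent in person:
- Face-to-face: (60 + 240) / (60 + 240 + 40) = 300 / 340 = 88%.
- Semi face-to-face: 60 / (60 + 48 + 40) = 60 / 148 = 41%.

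This counts video sessions as not in person. The article gives only the video delivery and does not say whether anyone else is present.

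**Step 3. What this could do to capture (assumed values only).** Suppose events occur at the same rate per minute of exercise in both modalities.
- If no event outside in-person time is ever reported, capture is 88% against 41%. This is an extreme case.
- If half of those events are volunteered, capture is (300 + 20) / 340 = 94% against (60 + 44) / 148 = 70%.
- If every event is volunteered, capture is 100% in both.

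A second illustration uses 40 participants per modality and an assumed true risk of 20% in each. If 90% of events are noticed face-to-face and 50% semi face-to-face, the expected recorded counts are 40 × 0.20 × 0.90 = 7.2 and 40 × 0.20 × 0.50 = 4.0. With equal ascertainment at 90%, both are 7.2.

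**The case against.** The strongest reply is that Section 2.5.11 is broader than its last paragraph. A reader might infer that serious events interrupt participation only when caused by the intervention. The text does not support that: serious illness, injury or a wound can trigger interruption whatever the cause, suspension is open for any justified reason, and the modification rule has no causal test. All interruptions and modifications are documented. This stands, and it confines the gap to events that lead to neither.

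A reader might also infer that the protocol declares itself unable to judge cause. It does not. The Discussion says that "observed changes in the study variables may be influenced by the effects of other interventions", and Section 2.3.1 justifies the burnout scale "while acknowledging the limitations inherent in attributing potential changes exclusively to the psychoeducational intervention". Both concern changes in outcome measures, neither mentions harms, and the Discussion adds that the team will try to isolate the effect of PsicoFIT. Judging whether one injury arose in a football session is a different task. The caveats show only that the components run together.

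Third, the article does not say how adverse events are elicited or who judges relatedness. That may sit in the full protocol or in the parent programme, so its absence is not a fault. The semi face-to-face arm also has a weekly in-person hour, an offer of support when viewing is not reported, and a week-13 assessment in a computer lab. Unequal capture is therefore a risk and has not been shown.

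Finally, no comparison of safety between modalities is among the outcomes in Section 2.7 or the analyses in Section 2.6. This stands: no planned estimate is biased by the rule.

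What survives is a rule that the article does state. It filters on cause before recording and uses a term with two meanings.

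**Conclusion.** The point holds in a limited form. The duty to record and report an adverse effect depends on a prior causal judgement about an undefined intervention. An event judged unrelated to PsicoFIT that leads to no interruption or modification need not be recorded. This follows from the wording and needs no assumption beyond the ambiguity of the term.

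The imbalance in opportunity to notice events follows from the stated schedule: 6 to 1 in scheduled in-person time, and 88% against 41% of prescribed exercise time. Without uniform questioning, recorded harms would not be comparable between modalities. How far capture would differ cannot be had from the document. The figures in Step 3 rest on assumed event rates and reporting, and should not be read as estimates for this trial.

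The change is worth making because it is cheap and improves both safety information and comparability. It does not threaten the primary analysis.

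**What to change.** Rewrite the last paragraph of Section 2.5.11 so that all adverse events from week 1 to week 13 are recorded in both modalities whatever the suspected cause, with date, activity (PsicoFIT, football or video exercise, nutrition, other), seriousness and modality. Relatedness is then judged after recording.

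Put one identical adverse-event question to both arms in the weekly messages already sent (Section 2.5.9) and on the week-13 form, and report counts by modality. The weekly question matters most, because participants who leave will not reach week 13.

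Separately, state whether the intervention in Section 2.5.11 means PsicoFIT or the whole TIGREFIT programme, and reconcile the causal and non-causal triggers for interruption and modification. Which rule should apply is for the investigators and the ethics committee.

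The cost is one paragraph, one question in existing contacts, a simple log, and time to read replies and file more minor unrelated events. No new visits are needed. If the change counts as substantial, Section 2.8 requires ethics committee approval.

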### 2.6. Data Analysis

#### 2.6.1. Quantitative Analysis

Due to the practical limitations in following up with those participants who do not complete the program, the primary analysis will be conducted using a per-protocol approach [111], considering only those participants with complete data at baseline and at the end of the intervention; missing data will not be imputed.

This approach will allow for evaluating the changes associated with each intervention under real-world implementation conditions, acknowledging the anticipated risk of participant attrition and that the benefits of randomization may not be fully preserved, while reflecting its applicability in a pragmatic context.

All statistical analyses will consider a 95% confidence level (5% error), ensuring transparency and reproducibility.

Preliminary Analysis. Descriptive statistics for central tendency (mean, median), dispersion (standard deviation and variance), and distribution (skewness and kurtosis) will be estimated for each observed variable. Next, normality tests will be conducted, and the reliability of the instruments will be estimated by measuring their internal consistency through Cronbach’s alpha (α) and McDonald’s omega (ω) coefficients. Subsequently, bivariate correlation analyses will be performed to measure the strength and direction of the relationship between the variables.

Associations among motivational and outcome variables. To examine the associations between the coach’s controlling interpersonal style, basic psychological need satisfaction, autonomous motivation, healthy lifestyle, and burnout, hierarchical multiple regression analyses will be conducted. Separate models will be estimated for each intervention modality (face-to-face and semi face-to-face) and for each measurement occasion (baseline and post-intervention), with predictor variables entered in a theoretically driven manner [42]. Effect sizes and confidence intervals will be calculated to complement the statistical significance, and statistical power will be considered when interpreting the results [112].

Intervention-related changes. Changes in the coach’s controlling interpersonal style, basic psychological need satisfaction, autonomous motivation, healthy lifestyle, and burnout from baseline to post-intervention will be examined. Within-group pre-post comparisons will be conducted for each intervention modality (face-to-face and semi-face-to-face). Between-group comparisons will assess whether the magnitude of changes differs between the two modalities [42]. Effect sizes will be calculated to quantify the magnitude of the observed changes, and statistical power will be considered in interpreting the results [113].

Mediation effects. The effects of basic psychological needs satisfaction and autonomous motivation as mediating variables (the mediation effect of basic psychological needs satisfaction and autonomous motivation on the relationship between the coach’s controlling interpersonal style, healthy lifestyle, and burnout, as well as the effect of basic psychological needs satisfaction on the relationship between autonomous motivation, healthy lifestyle, and burnout) will be evaluated using regression-based mediation analyses with bootstrapping procedures to estimate direct and indirect effects following Hayes’s recommendations [43], considering pre- and post-intervention data. The significance of mediation inferred when the confidence interval of the indirect effect does not include zero allows for the assessment of whether the observed relationships are explained directly or indirectly through the proposed mediating variables. Mediation effects will be considered exploratory due to the sample size and the nature of the study.

Moderation Effects. The moderating effects of both intervention modalities will be evaluated using regression-based moderation analyses, following Hayes’s recommendations [43], considering both pre- and post-intervention data. Moderation will be examined by including interaction effects, as evaluated through bootstrapped confidence intervals. Significant interaction effects will indicate that the strength or direction of the relationship between predictors and outcomes differs according to the intervention modality. Moderation effects will be considered exploratory due to the sample size and the nature of the study.

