#### 2.2.3. Inclusion, Exclusion, and Withdrawal Criteria

The inclusion, exclusion, and elimination criteria for this study will be based on those established by the TIGREFIT program [39].

Inclusion Criteria. Men and women aged 35 to 50 years, with a body mass index (BMI) between 28 and 34.9 kg/m^2^, performing less than 150 min of moderate to vigorous physical activity per week, with at least a secondary education level, access to medical health services, and who provide consent to participate in the study and randomization.

Exclusion Criteria. Individuals with uncontrolled medical conditions, use of medications that significantly alter metabolism, diagnosis of severe psychiatric disorders, pregnancy or breastfeeding, recent or chronic musculoskeletal injuries that limit physical activity, participation in other weight loss or physical activity programs, excessive alcohol or psychoactive substance use, difficulties understanding the study language, or lack of time availability to follow the program.

Withdrawal Criteria. Participants who voluntarily withdraw from the program or those who fail to fully complete the evaluation instruments. 

The overall study procedure is presented in Figure 1.

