#### 2.2.5. Participant Retention

Strategies to promote retention in the study will include informational and engagement approaches. An induction session will be conducted to explain the details of the intervention and the schedule of activities, with the aim of reminding the participants of the expected benefits, the importance of their participation, and helping them organize their availability for the program.

Additionally, social incentives linked to Club Tigres will be offered, such as visits to training sessions, match tickets, or interactions with club players.

Participants who accumulate consecutive absences or fail to report viewing the video capsules, whichever the case, will be offered support to continue.

In the case of voluntary withdrawal, the participants will be given the possibility to rejoin the study if feasible; otherwise, they will be considered for future editions of the program.

If a participant leaves the study, their contact information and completed evaluations will be recorded. When possible, they will be asked to complete a survey regarding their experience and reasons for leaving.

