#### 2.5.9. Intervention Adherence

In the face-to-face modality, attendance at sessions will be recorded; to support adherence, reminders and weekly reinforcement messages will be sent to the participants. In the semi face-to-face modality, the participants will report the viewing of the capsules; to encourage adherence, the capsules will be sent with encouraging messages, reinforced with a reminder message, and the participants will submit a screenshot as evidence of capsule viewing.

Only those participants who will have completed both the baseline and post-intervention assessments will be included in the dataset, ensuring that the data reflect actual participation in the program.

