#### 2.5.10. Concomitant Care

Restrictions will be established regarding participation in other wellness programs that include psychological, nutritional, or physical activity interventions.

Continuation of any recreational physical activity already practiced by the participants before the study will be allowed, as well as the use of prescribed medications that do not affect variables such as motivation, well-being, or physical activity.

The participants may engage in psychological therapy as long as it does not specifically address motivation for physical activity or psychological well-being using approaches similar to the intervention.

If non-compliance compromising data validity is detected, it will be evaluated whether the participant should be excluded from the final analysis.

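### The primary analysis keeps only participants with complete questionnaires and calls this per-protocol, which leaves the modality comparison and the within-arm changes open to selective dropout

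*Protocol article*

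**What the plan says.** Participants are randomised to face-to-face or semi face-to-face delivery, 40 per modality (sections 2.1 and 2.2.4). Both primary outcomes, healthy lifestyle and burnout, are analysed as post-intervention minus baseline score (section 2.7.1), within each modality and between modalities (section 2.6.1).

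On the analysis set, section 2.6.1 says that "the primary analysis will be conducted using a per-protocol approach [111], considering only those participants with complete data" at baseline and at the end, and that "missing data will not be imputed". The reason opens the same sentence: "Due to the practical limitations in following up with those participants who do not complete the program". The text then accepts the weakness, "acknowledging the anticipated risk of participant attrition and that the benefits of randomization may not be fully preserved".

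Section 2.5.9 records attendance in one modality and capsule viewing in the other. It uses neither to define the set: only people who have "completed both the baseline and post-intervention assessments will be included in the dataset, ensuring that the data reflect actual participation in the program".

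Section 2.2.5 says that leavers' contact details and completed evaluations are kept and that, where feasible, "they will be asked to complete a survey regarding their experience and reasons for leaving".

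**The concern.** A per-protocol set is normally defined by adherence to the assigned intervention. Here a person who attended nothing but filled in both rounds is included, while a person who took part in all 12 modules but missed week 13 is excluded. The set does not measure participation, and it gives up the comparison of the groups as randomised.

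The modality contrast is the only randomised comparison in the study. There is no untreated group, so the within-arm changes in Hypothesis 2 have nothing else to guard them against selection. If those who benefit less leave more often, completers improve on average even when the programme does nothing. If that selection is stronger in one modality, a difference between modalities appears. The article describes no analysis of all randomised participants alongside the completers' analysis.

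**Working it through.** **Is unequal dropout plausible?** Weekly minutes from sections 2.4.2, 2.4.3 and 2.5, taking the nutrition capsules as weekly (an assumption):

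- Face-to-face: 60 + 2 × 120 + 40 + 30 (nutrition) + 30 (PsicoFIT) = 400.
- Semi face-to-face: 60 + 2 × 24 + 40 + 5 + 5 = 158.

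The burden differs by a factor of about 2.5. Sections 2.6.1 and 3 expect attrition but give no rate, SD or pre–post correlation, so every rate below is an assumption. There is no stated figure to reproduce. The true effect is set to zero and results are in SD of the score.

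**Scenario A: dropout follows the unobserved change.** Loss d = 20% in one arm and 40% in the other; dropout propensity correlates 0.5 with change; pre–post r = 0.5, so the SD of change is √(2 − 2 × 0.5) = 1. The completers' mean change is 0.5 × φ(z_d)/(1 − d).

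- d = 0.20: 0.280/0.80 = 0.350; × 0.5 = 0.175.
- d = 0.40: 0.386/0.60 = 0.644; × 0.5 = 0.322.
- Spurious modality difference: 0.322 − 0.175 = 0.147.

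**Scenario B: dropout follows baseline in one arm.** Low scorers leave one arm (40%, correlation 0.5); 20% leave the other at random. The completers' baseline in the first arm is 0.5 × 0.644 = 0.322 too high, and their change is (r − 1) × 0.322.

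- r = 0.5: −0.161.
- r = 0.7: −0.097.

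The other arm's bias is 0, so these are also the between-modality biases.

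**What the alternatives recover** (large-sample simulation, r = 0.5):

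| | Completers' change score | Completers, baseline-adjusted | All randomised, likelihood under missing at random |
|---|---|---|---|
| A, between modalities | 0.147 | about 0.11 | about 0.116 |
| A, within arm | 0.18 and 0.32 | – | 0.14 and 0.25 |
| B, between modalities | −0.16 | 0.00 | 0.00 |
| B, within the affected arm | −0.16 | – | 0.00 |

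In B, adjustment among completers alone already removes the between-modality bias. Adding leavers' baselines matters mainly for the within-arm change. In A, no model built on the observed scores removes most of the bias; only outcome data from leavers can.

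**Equal dropout is not safe for within-arm change.** If leavers' mean change is D worse than completers', the within-arm bias is D × d. With D = 0.5 and d = 0.20 it is 0.10 SD in each arm, although the between-modality bias is then 0.

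**The case against.** The authors disclose the problem in section 2.6.1 and list attrition bias among the limitations in section 3. That is a fair point about candour, but it leaves the primary set unchanged.

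The bias may also be smaller. With one dropout mechanism in both arms, loss of about 25% against 34% and r = 0.6, the completers' modality bias is only 0.03 to 0.07 SD. And in Scenario A an all-randomised model leaves most of the bias in place. Both points stand: the size is uncertain, and modelling alone is not a full remedy.

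Four stronger readings are tempting, and the documents do not support them.

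- A reader might infer that one blank item removes a participant, because section 2.2.3 withdraws "those who fail to fully complete the evaluation instruments". No item-level rule is stated. The forms are electronic (section 2.3.4) and may or may not force answers, and such rules are commonly left to an analysis plan.
- A reader might infer that the authors concede a non-randomised comparison. They say only that its benefits might not be fully kept.
- A reader might see a flat contradiction between the stated follow-up limits and the exit survey. The survey is conditional on feasibility, so the two are compatible; it shows only that some leavers may be reachable.
- A reader might take section 2.5.10, where "it will be evaluated whether the participant should be excluded from the final analysis", as a licence to exclude after seeing outcomes. It is tied to breaches of the concomitant-care restrictions that threaten data validity, and nothing says outcomes are seen first.

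**Conclusion.** The point holds on the definition, the rationale and the choice of primary set. A set defined by complete questionnaires is called per-protocol, and the claim that it reflects actual participation is wrong. Used as the primary set with unadjusted change scores, it exposes both primary outcomes to selective dropout, between modalities and within each.

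Under the assumed 20% against 40% loss and correlation of 0.5, the between-modality bias is about 0.15 to 0.16 SD in magnitude. It can favour either arm, depending on who leaves. These are illustrations: the documents fix neither size nor direction, so the results may, not will, be distorted.

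**What to change.** - Make the primary analysis all randomised participants in the assigned modality, with post-intervention scores adjusted for baseline and all available data used. A likelihood model does this without imputation.
- When leavers are reached for the exit survey, ask them to complete the lifestyle and burnout questionnaires at week 13. This step matters most, because modelling cannot replace it if dropout follows unobserved change. Section 2.3.4 places the instruments in a computer lab, so remote completion would have to be added.
- Keep a per-protocol set as supplementary, defined in advance by modules attended or capsules viewed.
- Correct the claim about actual participation in section 2.5.9.
- State what the repair can and cannot do: adjustment removes the bias when dropout depends on baseline (0.16 to 0.00 SD, mostly from the adjustment itself) but leaves most of it otherwise (0.147 to about 0.116 SD). Participants who leave before week 2 have no burnout baseline, because section 2.3.3 first measures burnout then.

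The cost is protocol wording, slightly more analysis and a remote route for two questionnaires. The estimate will include poorly adherent participants and may be smaller.
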